## Abstract

University students’ mental health has become a public health issue since increasingly students report high levels of psychological distress. Mental health difficulties influence students’ lives, such as academic performance, relationships satisfaction, and quality of life. Moreover, different kinds of obstacles often hinder help-seeking behavior. Such evidence strongly suggests the need to implement prevention and promotion strategies to increase health and well-being in educational contexts. This article presents a study protocol for implementing and evaluating NoiBene, an evidence-based group intervention that aims to promote mental health and well-being, improve a series of transversal competencies (e.g., emotional awareness, commitment to values, assertiveness, goal setting), and decrease dysfunctional transdiagnostic mechanisms (i.e., perfectionism, repetitive thinking, experiential avoidance). A randomized controlled trial will be conducted to evaluate the protocol’s efficacy. Participants will be assigned to one of the three conditions: the NoiBene Group condition (NB-G), the NoiBene guided web-based condition (NB-WB), or the waiting list condition (WLC). The NB-G intervention consists of six face-to-face group meetings, each dedicated to specific issues related to well-being or vulnerabilities. Every meeting includes an explanation of the theoretical contents, individual and group exercises, and role-plays. The NB-WB intervention covers the same topic addressed in the NB-G intervention. In this case, participants carry out a series of online modules, including theoretical explanations, practical exercises, useful activities, and self-monitoring tools. Students will individually meet the Tutor once every 2 weeks. The primary outcome will include an increase in mental health and well-being. Secondary outcomes will include changes in emotional awareness, assertiveness, perfectionism, rumination, worry, self-criticism, experiential avoidance, and academic performance and satisfaction. We expect that participants in both NoiBene conditions will show these outcomes. However, we hypothesized that the NB-G conditions will be more effective than the NB-WB in improving assertiveness. Besides treatment efficacy, we expect that students can benefit from the NB-G or NB-WB differently based on their specific behavioral and motivational patterns. Outcomes will be assessed at pre-, post-intervention and 6-months follow-up. In conclusion, we believe that NoiBene is a promising tool that can improve students’ well-being, and it could have positive implications for preventing mental health disorders among students.

## Introduction

The last decades have been characterized by a growing interest in university students’ mental health. Several studies have amply demonstrated that psychological distress is growing among students worldwide and that a substantial number of university students meet the criteria for different mental disorders during their university years (see Sharp and Theiler, 2018 for a review). Given that most mental disorders first appear in early adulthood, particularly between 17 and 24 years (Kessler et al., 2007; De Girolamo et al., 2019), it is not surprising that data from many epidemiological studies show high levels of psychological problems among college students. Furthermore, attending university can be a stressful experience for many students that can find themselves having to cope with academic pressure and new adult-like responsibilities (Pedrelli et al., 2015; Auerbach et al., 2018; Mortier et al., 2018). High levels of psychological distress are associated with substantial impairment in academic performance (Auerbach et al., 2016; Bruffaerts et al., 2018) and represents a risk factor of dropping out of studies (Kitzrow, 2003; Ishii et al., 2018). Furthermore, mental health problems can increase vulnerability to suicidal thoughts and behaviors (Mortier et al., 2018). Despite high levels of psychological disease, many students rarely ask for help. The low rate for seeking treatment could be due to several factors that constitute the principal barriers to treatment, such as, high costs required for psychological support, stigma or self-stigma, poor mental health literacy and shortage of mental health services (Eisenberg et al., 2007, 2009). Poor help-seeking behavior is a cause of concern especially considering that untreated psychological disorders can lead to a worse outcome (Kisely et al., 2006; Ricky and O’Donnell Siobhan, 2017) and could have a long-term negative impact on a student’s quality of life.

Based on this evidence, the psychological distress that students experience can be considered a public health issue. Moreover, the recent COVID-19 outbreak impacted higher education, forcing once the closure of educational institutions and then the respect of rules such as social distancing and the use of masks (de Oliveira Araújo et al., 2020). The COVID-19 pandemic and the stringent rules to contain the virus spread had deleterious effects on students’ mental health. Indeed, many students reported an increased level of stress, anxiety, and depression during the COVID-19 pandemic (Dawson and Golijani-Moghaddam, 2020; Charbonnier et al., 2021; Di Consiglio et al., 2021b; Fernández-Castillo, 2021; Le Vigouroux et al., 2021). These data are particularly relevant if we consider the students’ mental health conditions before the pandemic (Sharp and Theiler, 2018). The increasing psychological distress showed by students during and after the pandemic reinforced still more the need to improve strategies to promote students’ mental health and prevent mental disorders. As suggested by the World Health Organization (WHO), mental health is not just the absence of mental disorders but is a state of well-being in which the individual can realize his/her-self and cope with the daily demands (World Health Organization [WHO], 2018). From this perspective, mental health promotion and prevention are necessarily related and overlapping: mental health is promoted by increasing well-being and enhancing transversal competencies, and mental disorders are prevented by reducing risk factors (Lahtinen et al., 1999; Saxena et al., 2006). University is an essential part of any health promotion and prevention strategy: it can develop a culture that supports mental health, it can provide students with mental health service, and it can build an environment that facilitates help-seeking behavior (Tsouros et al., 1998; Hughes and Spanner, 2019). For example, to promote well-being in the educational context, the World Health Organization [WHO] (1994) has focused on developing and/or strengthening a series of cognitive, emotional, and relational transversal skills, also called life skills. Life skills include making decisions and solving problems, critical and creative thinking, communication and interpersonal relationships, self-awareness and empathy, and emotion regulation. A broad range of evidence suggested the effectiveness of life skills training among university students in reducing the impact of stressful events, in increasing mental health (Savoji and Ganji, 2013), emotional intelligence (Lolaty et al., 2012), happiness, quality of life and emotion regulation (Mohammadkhani and Hahtami, 2011), in preventing drugs abuse behaviors (Moshki et al., 2014), in decreasing anxiety and depression symptoms (Sobhi-Gharamaleki and Rajabi, 2010).

In line with these considerations, the last decades have been characterized by a growing spread of promoting and preventing intervention among university students (Conley et al., 2013; Cuijpers et al., 2021). For example, but not limited to, such interventions are effective in increasing positive mental health and decreasing depression and anxiety symptoms (Bendtsen et al., 2020), in reducing distress (Galante et al., 2018), in promoting self-compassion, social connectedness, resilience, and flourishing (Long et al., 2021) and in enhancing self-acceptance, positive relations with others, optimism, and self-esteem (Marrero et al., 2016). Most of these interventions have been developed to overcome the costs and the limits of the traditional form of intervention, such as one-to-one in-person treatment, provided in a clinical setting and administered by a highly trained mental health professional (Kazdin, 2019). More specifically, these models of treatment, generally developed as internet-based intervention or group intervention, can reach a more significant number of people, and could represent an effective solution to address the issue of mental health among students. Both internet-based intervention and group intervention have a series of advantages: internet-based intervention, generally delivered *via* computer or smartphone, allows access to a series of resources at any time and from all places, speedily and easily; it guarantees anonymity, privacy, and confidentiality and it is a low-priced tool (Barak and Grohol, 2011; Montagni et al., 2020). Moreover, internet-based intervention is particularly leading among young people, especially students, since they represent one of the largest consumers of digital devices (Lenhart et al., 2010). As well as that previously described, group interventions are generally cost-effective; consequently, they can increase the accessibility to services and reduce barriers to treatment. Moreover, unlike internet-based interventions, they have the advantage of allowing students to interact with others and to promote relationships between group members working together toward common goals. Some factors, such as socializing techniques and interpersonal learning that are crucial elements of group interventions (Yalom, 1985), may be essential for university students to improve social skills to develop more positive and effective relationships, both in personal and professional contexts. Several studies have shown that group interventions in college students are effective for the treatment of depression (Church et al., 2012), for the development of resilience and coping techniques (Houston et al., 2017), for facilitating the transition of students to the first year of university (Oppenheimer, 1984), to promote social support, self-efficacy, understanding of one’s own and other’s emotions (Ando, 2011). As exposed, both modalities have a series of advantages, however, although to some extent effective, most of these programs focus on specific issues or disorders, thus underestimating the relevance of comorbidity among mental disorders (Kessler et al., 2005; Roca et al., 2009; Nock et al., 2010), between mental and medical conditions (Alegria et al., 2001; Daré et al., 2019; Kelly et al., 2019) and the interaction among risk factors, protective factors, and stressful events (Belsky and Pluess, 2009). Moreover, such interventions foster a mechanistic view of the understanding of the human being, which contrasts with the biopsychosocial model of health and the development of personalized interventions (Frazier, 2020). For these reasons, a change of strategy appears necessary. Such interventions should aim to globally promote health and psychological well-being, in terms of individual’s resources, abilities and strengths, together with a transdiagnostic approach (Mansell et al., 2009): it can be helpful in early intercepting psychopathological trajectories and prevent the risk of developing mental disorders and psychological distress. Based on these considerations, we developed NoiBene, a comprehensive and wide-ranging intervention that aims to promote well-being and prevent various forms of psychological distress by targeting some of the main risk and maintaining factors for mental disorders (Di Consiglio et al., 2021a). NoiBene has been developed on evidence-based approaches such as Positive Psychology (Seligman et al., 2005), Cognitive–Behavioral Therapies (CBT; Dobson and Dobson, 2018), and Nonviolent Communication (NVC; Rosenberg and Chopra, 2015). Positive psychology promotes adaptive human functioning by fostering positive emotions, behaviors, and character strengths that allow individuals to build a life of meaning and purpose (Seligman et al., 2005). CBTs, especially Acceptance and Commitment Therapy (Hayes et al., 2009) and Self-Compassion Therapy (Gilbert, 2009), are expanding their target from the mere reduction of symptomatology to the development of skills that contribute to mental health and well-being, such as self-acceptance and commitment to personal values. Lastly, NVC is a method based on judgment-free observation and recognition of feelings and needs that aim to promote empathic communication fostering positive interpersonal relationships (Rosenberg and Chopra, 2015). NoiBene integrates these theoretical and intervention models: the aim is to operate according to a promotion and prevention approach. Especially, the program aims (1) to improve mental health and well-being, (2) to increase positive and flexible behaviors, (3) to improve those life skills mainly related to psychological well-being and self-realization (e.g., emotional awareness, assertive communication, goal setting), (4) to promote the commitment to the satisfaction of personal needs and values, (5) to enhance strategies to adequately handle academic challenges, (6) to weaken some of the main risk and maintaining factors for mental disorders (i.e., repetitive thinking, perfectionism and experiential avoidance).

### Aim and Scope

The purpose of this paper is to present the research protocol and recruitment process that will be employed for a randomized controlled trial (RCT) to evaluate the efficacy of NoiBene as a group intervention (NB-G). This condition will be compared with two other conditions: NoiBene as a guided web-based intervention (NB-WB) and with a waiting list condition (WLC). We hypothesized that participants in the NoiBene conditions (both NB-G and NB-WB), compared with participants in the WLC, would show after the intervention higher levels of mental health and well-being (Cuijpers et al., 2021) as well as an increase in academic performance and satisfaction (Bean and Eaton, 2001). We also predict that students in the NoiBene conditions will increase their emotional awareness and assertiveness, and they will reduce the level of perfectionism, repetitive thinking, and experiential avoidance (Di Consiglio et al., 2021a). However, we hypothesized that the NB-G conditions will be more effective than the NB-WB in improving assertiveness, since the group context guarantees more supervised practice (Salas and Cannon-Bowers, 2001; Gresham, 2002; Taylor et al., 2005), and it ensures a positive environment where the member can interact in an adaptive manner (Yalom, 1985). However, besides treatment efficacy, we expect that students can benefit from the NB-G or NB-WB differently based on their specific behavioral and motivational patterns. For example, bases on specific personality traits or set of values students could be more motivated to participate and benefit more from a guided web-based intervention or from a group intervention.

## Methods

### Participants

Seventy-five (*n* = 75) students will be voluntarily recruited from different universities in Rome, Italy. The sample size for this study was determined based on power analysis using G*Power 3.1.9.7 (Faul et al., 2007). We calculated that the minimum required sample size to detect an effect size of *f* = 0.25 using a mixed analysis of variance (ANOVA) including within-subject (3-time points) and between-subject (3 groups) effects with 95% power and at a two-sided 5% significance level was 54 participants (18 per treatment arm). However, attrition is a common problem that occurs in RCT: around 20% of participants withdraw before completing the study protocol (Mason, 1999). In conclusion, we plan to recruit approximately 75 participants (25 per treatment arm).

NoiBene will be advertised by word of mouth, mailing lists, and sharing fliers on various social networks (i.e., Facebook, Instagram). Students will be informed about the implementation of a group intervention to promote well-being and to prevent psychological distress. They will receive information about the program and about the specific goal of the intervention. The organization and the calendar of the meetings will also be presented. Since many university courses include credits achievable by practical activities (highly specialized workshops), all participants will receive an intervention completion certificate that they can use to achieve such credits.

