### Procedure

This study was approved by the Ethics Committee of the Department of Psychology, Faculty of Medicine and Psychology, Sapienza University of Rome (code n. 0001443). Students who desire to participate in the NoiBene have to send an email to ask for participation. Before starting the study, participants will have to provide informed consent after reading about the goals and procedure of the study and information about data protection and privacy according to the General Data Protection Regulation (EU) 2016/679 (GDPR). Participation will be voluntary, and every participant will be free to withdraw at any time. Once achieved the consent, to detect clinical disorders, students will ask to answer an online survey containing MCMI-III and SCL-90-R questionnaires. According with the exclusion criteria, if no significant clinical condition is suggested, participants will be randomly placed into one of the three conditions: the NoiBene group intervention (NB-G), the NoiBene guided web-based intervention (NB-WB), and a waiting list condition (WLC). Before and after the intervention, a series of standardized questionnaires will be administered to participants of both groups to assess the mental health and well-being (PWBI and WEMWBS), emotional awareness (TAS-20), assertive communication (SIB), perfectionism (MPS), rumination (RRS), worry (PSWQ), self-criticism (LOSC), and experiential avoidance (AAQ-II). Moreover, an *ad hoc* questionnaire will be administered to evaluate academic performance and satisfaction with the program. The same assessment will be repeated 6 months after the end of the intervention. Moreover, since therapeutic and group relationships are a powerful non-specific element that predicts outcome in individual (Lambert and Barley, 2001) and group interventions (Johnson et al., 2005), to monitor the therapeutic and group relationship, the WAI-I and the GQ will be administered to participants in the NB-WB and NB-G conditions, respectively. Figure 1 shows the recruitment and study procedure.

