#### Waiting List Condition

Students in this condition will not receive any intervention. After the study will be ended, the waiting list participants will be invited to take part in the intervention. Participants randomized to the WLC will be offered to choose their preferred treatment after completing follow-up measurements. However, the beginning of the group intervention depends on whether the minimum number of participants is reached. So, we will inform students that if we do not receive at least 10–12 requests of participation, they will have only the opportunity to be included in the guided web-based intervention.

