Moreover, we believe that the group protocol could be even more effective than the guided web-based protocol in improving assertiveness (Conley et al., 2013), since the group protocol ensures supervised skills practice over multiple sessions, an essential component of successful training (Salas and Cannon-Bowers, 2001; Gresham, 2002; Taylor et al., 2005). Moreover, some unique characteristics of the group can foster this positive change. For example, the group ensure a positive environment where the member can interact in an adaptive manner and can engage in positive relationship; also, the group context ensure the modeling process both from the Tutor and from other member and imitative behaviors are an important source of learning (Yalom, 1985; Johnson et al., 2005) unlike the individual guided intervention. However, we believe that it is important to consider that students can benefit from the NB-G or NB-WB differently based on their specific behavioral and motivational patterns. For example, values are an important broad motivator of actions and affect prosocial behavior (Schwartz, 1992). Values such as benevolence and conformity promote cooperative and supportive social relations. Indeed, these values motivate actions to promote the welfare of others and to avoid adverse outcomes for self. Conversely, values such as security and power usually oppose prosocial behavior since they motivate to maintain a stable and protective environment and emphasize self-interest (Schwartz, 2010). Students guided by such values could be more motivated to participate and benefit more from a group intervention or from a guided self-help intervention, respectively. This consideration is significant if we also consider the clinical utility of these interventions. This dimension concerns the extent to which the intervention will be effective in a real-world practical setting (American Psychological Association, 1995). Moreover, when proposing an intervention, it is important to consider not only the best available intervention but also the individual characteristics and preferences (American Psychological Association Presidential Task Force on Evidence-Based Practice, 2006). Therefore, outside a controlled empirical context, we expect that students will report a preference toward a group or guided self-help intervention based on personal characteristics.

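### Recruitment describes only a group intervention, yet applicants are randomised to group, web or waiting list; this may modestly favour the group arm over the web arm

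*Protocol article*

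**What the plan says.** Under Participants, the protocol article describes what prospective students are told: "Students will be informed about the implementation of a group intervention to promote well-being and to prevent psychological distress". They also receive information about the programme and its goal, and "The organization and the calendar of the meetings will also be presented". Neither the web-based arm nor the waiting list appears in that description. All participants are offered a completion certificate that can count towards course credits.

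Under Procedure, entry is by self-referral: "Students who desire to participate in the NoiBene have to send an email to ask for participation". Next, "participants will have to provide informed consent after reading about the goals and procedure of the study". After online screening, "participants will be randomly placed into one of the three conditions".

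The arms differ in how far they match the message. NB-G has six in-person group meetings. NB-WB covers the same topics through online modules, with an individual video call with a tutor every two weeks and no group meetings. Of the WLC the article says: "Students in this condition will not receive any intervention". After follow-up these students may choose a format, but with a condition attached: "if we do not receive at least 10–12 requests of participation, they will have only the opportunity to be included in the guided web-based intervention".

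Aim and Scope names the recruitment process as one of the subjects of the paper. It also suggests, as an example, that motivation and benefit could depend on format. Expected Results and Discussion adds that "we expect that students will report a preference toward a group or guided self-help intervention based on personal characteristics", although that sentence is expressly about practice outside a controlled study.

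**The concern.** Students choose whether to apply after hearing about a group and its dates. If format affects motivation, as Aim and Scope suggests it could, a message naming one format will tend to attract students who want that format. About two thirds of them are then allocated to something else, and they know it. The efficacy outcomes are self-report questionnaires.

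The comparison most exposed is NB-G versus NB-WB, and within it the directional hypothesis that the group improves assertiveness more, which is measured by a self-report scale. Disappointed web-arm students may engage less, leave more often or rate themselves lower, and each of these would look like an advantage of the group format. Students who prefer web delivery would also be under-represented, which limits what the trial can say about who suits which format. The assessments listed under Procedure and the models under Statistical Analysis include no measure of format preference, so the size of the problem could not be judged afterwards.

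**Working it through.** **1. The plan's own figure.** The article gives a minimum of 54 (18 per arm) for a mixed ANOVA with 3 groups and 3 time points, f = 0.25, 5% level and 95% power. The correlation between repeated measures is not stated, so 0.5 is assumed here. For the group-by-time interaction:

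- λ = f² × N × m / (1 − ρ) = 0.0625 × 54 × 3 / 0.5 = 20.25
- df1 = (3 − 1)(3 − 1) = 4; df2 = (54 − 3)(3 − 1) = 102
- power = 0.958, and 54 is the smallest multiple of 3 that reaches 95%. With ρ = 0.3 the number is 72; with ρ = 0.7 it is 33.

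For 20% loss, 54 / 0.8 = 67.5, so 68 are needed. The planned 75 tolerates a loss of 1 − 54/75 = 28%.

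**2. Is power the problem?** Assume strongly unequal drop-out: 10% in NB-G and 40% in each of the other arms. About 22, 15 and 15 students complete, 52 in all, and nominal interaction power at ρ = 0.5 is still about 0.95. The issue is therefore possible bias, not lost power.

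**3. NB-G versus NB-WB.** Let p be the share of recruits who prefer the group and d the average cost of a mismatch on a self-report score. The documents give neither. Randomisation makes p the same in each arm in expectation. The mismatched share is p in NB-WB and 1 − p in NB-G, so the spurious difference is (p − (1 − p)) × d = (2p − 1) × d. With d = 0.2 SD assumed:

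| p (assumed) | Mismatched of 25 in NB-WB / NB-G | Spurious difference |
|---|---|---|
| 50% | 12.5 / 12.5 | 0 |
| 60% | 15 / 10 | 0.2 × 0.2 = 0.04 SD |
| 80% | 20 / 5 | 0.6 × 0.2 = 0.12 SD |
| 90% | 22.5 / 2.5 | 0.8 × 0.2 = 0.16 SD |

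For scale, the standard error of an unadjusted difference between two arms of 25 is √(2/25) = 0.28 SD.

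**4. Drop-out.** If a mismatch adds 10–20 percentage points of drop-out (assumed) and p = 80%, the addition is 0.80 × 10–20 = 8–16 points in NB-WB and 0.20 × 10–20 = 2–4 points in NB-G, a gap of 6–12 points. At p = 60% the gap is 2–4 points; at p = 90% it is 8–16.

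**5. NB-G versus WLC.** Every WLC student goes without an intervention during the trial, whatever the advert says. On the same model the difference is (1 − (1 − p)) × d = p × d.

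- p = 80%: 0.80 × 0.2 = 0.16 SD
- p = 50% (an advert that does not tilt preference): 0.50 × 0.2 = 0.10 SD
- part due to the advert: 0.16 − 0.10 = 0.06 SD

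Most of the WLC effect would remain under neutral wording.

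**The case against.** There is a fair case that this is minor.

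- **Consent comes before randomisation.** Students read the study's goals and procedure first, so they probably learn of the three arms and can decline. This stands: it should reduce surprise and remove some unwilling students. It does not bring back those who never applied because they wanted an online programme.
- **The recruitment text is condensed.** The flyer and e-mail are not shown, and students also receive information about the programme. This stands in part. The actual material may say more, but the article sets out to present the recruitment process, and the content it states names only the group.
- **Students may apply for other reasons.** The credit certificate is independent of format, and NB-WB still delivers NoiBene, with tutor contact. This stands. Over-selection of group-seekers is an inference and its strength is unknown.
- **The calendar is needed.** Anyone may be allocated to the group, so all must be able to attend. This stands, and the calendar should stay.
- **The trial is mainly about the group format.** Recruiting students who are willing to attend a group suits that aim. This is reasonable for NB-G itself, but does not protect the comparison with NB-WB.

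A reader might infer more: that the arms are confounded, that the comparison with WLC is seriously distorted by the advert, or that the authors themselves expect preference to drive results within the trial. The documents do not support these readings. Allocation is random, disappointment in WLC mostly comes with any waiting list, and the expectation about preference in Expected Results and Discussion concerns practice outside a controlled study. Aim and Scope supports only the milder statement that motivation could depend on format.

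**Conclusion.** The point holds in a limited form. The stated recruitment message names one of three possible allocations, in a trial where students know their arm and report their own outcomes. It may over-select students who want the group and so modestly favour NB-G over NB-WB through engagement, drop-out or self-rating, including on assertiveness.

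The illustrative 0.04–0.16 SD rests on two assumptions with no source in the documents: that 60–90% of recruits prefer the group, and that a mismatch costs 0.2 SD. Even the upper end is below the 0.28 SD standard error of the two-arm difference. Neither the sample size nor nominal power is called into question. This is a cheap improvement, best made before recruitment, because neither the selection nor an unrecorded baseline preference can be recovered later.

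**What to change.** 1. Reword the recruitment message neutrally: a study of the NoiBene programme in which students are assigned by chance to group meetings, an online programme with a tutor, or a waiting list, with the length of the wait stated.
2. Present the meeting calendar as an availability condition for taking part, not as the offer.
3. Add one item on preferred format to the online survey completed before randomisation. Report it descriptively by arm, examine drop-out by whether the allocation matched the preference, and name it in advance as a baseline covariate.
4. Label any preference-by-arm analysis exploratory. If 80% prefer the group, each arm has only about 0.20 × 25 = 5 students with the minority preference before drop-out, too few to be informative.

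The cost is new flyer and e-mail wording, a minor ethics notification, one extra survey item and possibly slower recruitment. The arms and sample size do not change.
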